## Abstract

**Background:**

Inappropriate prescribing of antibiotics for acute respiratory infections at the primary care level represents the major source of antibiotic misuse in healthcare, and is a major driver for antimicrobial resistance worldwide. In this study we will develop, pilot and evaluate the effectiveness of a comprehensive antibiotic stewardship programme in China’s primary care hospitals to reduce inappropriate prescribing of antibiotics for acute respiratory infections among all ages.

**Methods:**

We will use a parallel-group, cluster-randomised, controlled, superiority trial with blinded outcome evaluation but unblinded treatment (providers and patients). We will randomise 34 primary care hospitals from two counties within Guangdong province into the intervention and control arm (1:1 overall ratio) stratified by county (8:9 within-county ratio). In the control arm, antibiotic prescribing and management will continue through usual care. In the intervention arm, we will implement an antibiotic stewardship programme targeting family physicians and patients/caregivers. The family physician components include: (1) training using new operational guidelines, (2) improved management and peer-review of antibiotic prescribing, (3) improved electronic medical records and smart phone app facilitation. The patient/caregiver component involves patient education via family physicians, leaflets and videos. The primary outcome is the proportion of prescriptions for acute respiratory infections (excluding pneumonia) that contain any antibiotic(s). Secondary outcomes will address how frequently specific classes of antibiotics are prescribed, how frequently key non-antibiotic alternatives are prescribed and the costs of consultations. We will conduct a qualitative process evaluation to explore operational questions regarding acceptability, cultural appropriateness and burden of technology use, as well as a cost-effectiveness analysis and a long-term benefit evaluation. The duration of the intervention will be 12 months, with another 24 months’ post-trial long-term follow-up.

**Discussion:**

Our study is one of the first trials to evaluate the effect of an antibiotic stewardship programme in primary care settings in a low- or middle-income country (LMIC). All interventional activities will be designed to be embedded into routine primary care with strong local ownership. Through the trial we intend to impact on clinical practice and national policy in antibiotic prescription for primary care facilities in rural China and other LMICs.

**Trial registration:**

ISRCTN, ID: ISRCTN96892547. Registered on 18 August 2019.

## Background

Inappropriate use of antibiotics is a major contributor to the global public health challenge of antimicrobial resistance, and has been widely documented in the world, especially in low- and middle-income countries (LMICs) [1, 2]. Rising levels of antimicrobial-resistant infections may devastate our health system, costing many lives and using valuable resources [3, 4]. Acute respiratory infections (ARIs) are commonly seen in primary care consultations, with upper respiratory tract infections (URTIs) accounting for the largest source of inappropriate antibiotic use [5, 6]. This is because most URTIs are viral and self-limiting, and the administration of antibiotics is not clinically effective at shortening duration or symptom severity [7]. Similarly, among lower respiratory tract infections (LRTIs), acute bronchitis is commonly viral, but up to 80% of acute bronchitis patients still receive antibiotics [8]. Bacterial respiratory infections in primary care include acute otitis media, acute sinusitis and group A streptococcal pharyngitis and pneumonia, where narrow-spectrum antibiotics should be recommended as the first choice according to US [9] and UK guidelines [10]. However, broad-spectrum antibiotics, such as macrolides and fluoroquinolones, are often given which are more likely to generate resistance [11–13].

In China, inappropriate use of antibiotics is rampant and has raised national attention. This is particularly challenging in rural areas, as rural health workers have less education/training and may inappropriately prescribe more frequently [14]. A cross-sectional study in 10 provinces in Western China showed that antibiotics accounted for over half of the total prescriptions issued, and mostly for ARIs [15]. China has issued policies to regulate the use of antibiotics over the past 10 years. In 2012, the Chinese MoH issued a regulation for antibiotic prescriptions, limiting them to less than 60% of all prescriptions for inpatients and 20% for outpatients [16]. However, no operational details have been given. The policy has not been proven effective at improving appropriate antibiotic prescribing [17]. Additionally, the policy only focussed on large hospitals and neglected primary care facilities [18, 19].

Interventions addressing inappropriate antibiotic prescribing in primary care that only target patients often show no impact, while effective interventions have employed multi-component strategies that improve the knowledge, attitudes and behaviours of both healthcare providers and patients [20–22]. However, most intervention trials have been done in high-income countries [23, 24]. We previously developed an intervention to reduce inappropriate antibiotic prescribing for childhood (2–14 years old) upper respiratory tract infections (URTIs) in rural, public, primary care facilities known as township hospitals. The intervention included education for doctors and caregivers, as well as antibiotic prescribing peer-review meetings for doctors. We evaluated the intervention in a cluster-randomised controlled trial (cRCT) in Guangxi province, China, and it successfully reduced the frequency of antibiotic prescribing for childhood URTIs by 29 percentage points (95% CI − 42 to − 16) [25]. The interventions also demonstrated long-term benefits 12 months after trial completion [26].

The *WeChat* app is widely used in China. It allows multi-purpose messaging which can facilitate real-time communications among doctors, and between patients and doctors. This app has previously been effectively used in mass public health education programmes [27, 28]. In Tibet, we have employed the WeChat app to link with electronic medical records (EMR) and monitoring boxes to support tuberculosis patients in completing their treatment under harsh travel conditions [29]. However, these technologies have not been applied in reducing inappropriate use of antibiotics.

Based on our study in Guangxi, we aim to enhance our existing intervention by establishing an antibiotic stewardship programme in primary care facilities to address inappropriate prescribing of antibiotics for any form of ARI other than pneumonia, in patients of all ages, with the educational package targeting physicians and patients/caregivers. The intervention will incorporate the WeChat app and make use of EMR. Although the intervention is primarily focussed on public primary care facilities (where all data will be collected) we will also include a separate educational component addressing inappropriate prescribing of antibiotics by private village doctors who work in private village clinics. We will then pilot-test the intervention for feasibility and acceptability of the intervention and trial processes. Assuming feasibility and acceptability, we will then use a cRCT to evaluate the intervention’s effectiveness at reducing inappropriate prescribing of antibiotics for RTIs (and improving other outcomes) in outpatients of any age within public primary care facilities, in comparison to usual care (which means existing relevant standard processes only, as our previously developed intervention has only been implemented in the previous study sites).

## Methods

### Study design and setting

We will test the effectiveness of the intervention using a parallel, two-arm, cluster-randomised, controlled, superiority trial. We will run the trial in township hospitals of two rural counties in Shaoguan city, Guangdong province: Lechang and Nanxiong county. Shaoguan is in the north of Guangdong and remains one of the poorest areas in the province. In rural China primary care is provided by public township hospitals and private village clinics. Each township hospital covers 50,000 to 100,000 people and typically has less than 100 beds and 20–40 family physicians. *Family physicians* are medical doctors who receive formal medical training for either 3 or 5 years to practice acute care, and are employed by the township hospital. Village clinics are run by one or two paramedics (called *village doctors*), who receive limited medical training equivalent to a high-school level, and are guided by the township hospital. Village doctors are self-employed, primarily relying on three sources of income: the consultation fees paid by the rural health insurance, the Government’s public health package for preventative care, and income from private practice which is not properly documented.

Since 2013, the Chinese Government has implemented a ‘zero mark-up policy’, which prevents township hospitals and village clinics from earning profits by prescribing or dispensing medicines on the *Essential Medicines List*. Only medicines on the *Essential Medicines List*, issued by the national and provincial governments, can be prescribed in township hospitals and village clinics. These medicines are purchased through an open bidding platform run by the Provincial Government. Village clinics have access to a much lower variety of medicines compared to township hospitals. Formally, village doctors are not allowed to prescribe antibiotics based on their practice regulations. However, in our previous work in Guangxi we found that some village doctors did actually prescribe antibiotics for common colds, and that villagers often visited village clinics for convenience but frequently got the wrong advice, which is likely to drive demand for antibiotics when they seek care for themselves or their children in township hospitals [30]. For these reasons, village doctors need to be targeted by the invention as well.

### Eligibility criteria

#### Clusters

We define eligible clusters as all willing township hospitals, and family physicians in those township hospitals, that have functional and extractable EMR, along with their associated village clinics, and village doctors in those village clinics, from within the two selected counties of Shaoguan. However, the two township hospitals and their associated village clinics selected for the pilot study (see below) will not be eligible for the trial. Preliminary work suggests that all township hospitals and their associated village clinics within the two counties are eligible.

#### Patients

Our trial targets township hospitals, which provide the majority of primary care in rural China. Thus, we will collect all outcome data from eligible patients’ prescriptions issued within participating township hospitals. Similar to our previous trial setting, all outpatient consultations in China result in a prescription due to the request of health insurance scheme for documenting the consultation and the routine practice to give patients medications/herbs after the consultation. We will not collect prescriptions from village doctors because there is not sufficient documentation (such as prescriptions) available in private village clinics. We define eligible patients as outpatients aged between 0 and 75 years who receive a primary diagnosis of an ARI and receive a prescription following their consultation with a family physician in a township hospital. This includes a diagnosis of any URTIs according to the *International Classification of Disease, version 10* (ICD-10), and acute bronchitis as an uncomplicated acute lower respiratory tract infection (LRTI) (Table 1). However, patients and their prescriptions will not be eligible for inclusion in the trial if they are high-risk patients diagnosed with either: (1) non-ARIs, (2) pneumonia, as it is severe and clinically challenging to group with other uncomplicated ARIs (but we will extend the invention in the future to include pneumonia), (3) chronic conditions including asthma, chronic obstructive pulmonary disease, non-infective or non-acute disorders (e.g. cystic fibrosis, pulmonary embolus, heart failure, oesophageal reflux and/or allergies), non-respiratory infections (e.g. cutaneous infections, urinary tract infections, trauma-related infections, bacterial enteritis and/or cellulitis/abscess), immunological deficiencies, tuberculosis or any form of cancer.

**Fig. 1 Fig1:**
[figure not shown]
Detailed trial timeline. *Enrolment includes participating township hospitals signing the consent form and relevant healthcare staff being trained

**Table 1 Tab1:** *International classification of Diseases, version 10* (ICD-10) codes used for acute respiratory infection case definitions

Acute respiratory infections	ICD-10 codes
Acute nasopharyngitis (common cold)	J00
Acute pharyngitis	J02.8, J02.9
Acute tonsillitis	J03.8, J03.9
Acute URTIs of multiple and unspecified sites	J06
Acute bronchitis	J20
Acute sinusitis	J01.0, J01.1, J01.2, J01.4, J01.9
Acute otitis media	H65, H66, H67
Streptococcal pharyngitis	J02.0
Streptococcal tonsillitis	J03.0

*URTIs* upper respiratory tract infections

### Ethical approval

The trial has obtained ethical approval from the Ethics Committee of the First Affiliated Hospital of Guangzhou Medical University, China (2019–53) and the University of Toronto Office of Research Ethics, Toronto, ON, Canada (38265).

### Processes

#### Control arm

In control-arm clusters we will not make any changes or provide any input of any sort. Township hospital and village clinic providers will be allowed to continue treating patients with ARIs according to their existing usual treatment practices and guidelines, and as all data is collected from EMR there will also be no observable impacts for facility staff due to data collection.

#### Intervention

Based on our previous intervention we have developed a comprehensive antibiotic stewardship programme to reduce inappropriate prescribing of antibiotics for ARIs in the general population within rural primary care settings [25]. The intervention targets family physicians and patients in township hospitals, as well as the village doctors associated with township hospitals. The interventional activities are designed to fit within the existing policy requirements around antibiotic prescribing, which are detailed in Table 2. In all our training materials we define appropriate use of antibiotics as: (1) for all URTIs other than bacterial pharyngitis and sinusitis any use of antibiotics is considered inappropriate, and (2) for bacterial pharyngitis, sinusitis, otitis media and bronchitis, amoxicillin or penicillin are the first-line recommended antibiotics and are considered appropriate.

**Table 2 Tab2:** Intervention package and, where relevant, equivalent control-arm processes

Targeted group	Intervention arm	Control arm
Provider side	1. Improved antibiotic stewardship programme: (a) Each township hospital will establish an antibiotic stewardship working team including the township hospital director and a senior physician. The team will decide local antibiotic policies (b) The antibiotic stewardship team will hold peer-review meetings on antibiotic use monthly throughout the intervention period and embedded within the routine meetings of family physicians. Before each peer-review meeting, the antibiotic stewardship team will hold an internal meeting to prepare prescription reviews. The results will be sent to individual family physicians through WeChat. Each physician will see their performance of appropriate antibiotic prescribing against the hospital average (c) The antibiotic stewardship team will organise monthly peer-review meetings in township hospitals to ensure: (1) clear targets are set for appropriate use, (2) specific feedback is provided to high prescribers on improvement, (3) adjusting assessments for individual physicians based on their performance and (4) recording monthly meeting memos (d) The research team will make monthly supervisory visits to intervention township hospitals. The supervisory visits will ensure: (1) adherence to the interventional activities, (2) feedback and an opportunity to answer questions, (3) meeting with the antibiotic stewardship team to strengthen leadership and their commitment to reduce antibiotic prescriptions 2. Operational guidelines to reduce antibiotic prescribing for ARIs will be used. The guidelines will include patient symptom-based diagnostic algorithms, when to/ not to use antibiotics, and when narrow-spectrum antibiotics are preferred. Based on Chinese guidelines, chest x-ray examinations will be recommended when symptoms indicate pneumonia but clinical signs are not severe, or if a patient makes a second visit with signs indicative of pneumonia. Key health education messages during consultations with patients are also included (a) Every family physician in the township hospitals will receive an operational guideline both in printed and app-based form (b) Village doctors will receive a brief operational guide regarding appropriate use of antibiotics and referral 3. Systematic training including a half-day training workshop run by a county-level hospital senior physician and the research team will be given to family physicians and village doctors. This will involve: (a) Lectures, case discussions, role plays and Q&As on appropriate antibiotic prescribing practices for RTIs based on operational guidelines. Every family physician in the township hospitals will receive a training booklet both in printed and WeChat-app form (b) Using the WeChat app to monitor antibiotic use based on monthly reports from the EMR system to facilitate physicians’ discussions (c) Communication skills training when consulting with patients and/or caregivers 4. Improved electronic prescription system in the EMR to help township hospital family physicians make appropriate decisions when treating patients for RTIs, involving: (a) Embedded modules to encourage appropriate antibiotic prescribing practice, such as pops-up of laboratory test checklists and recommended antibiotics to prescribe when prescribing (b) An alarm system will be implemented to alert the family physician about any patient who re-visits any hospital within 14 days or who has been admitted within 1 month for a respiratory infection or sepsis after their index visit. In this scenario, chest x-ray and blood profile examinations will be recommended and recorded	1. Currently most township hospitals have an existing antibiotic stewardship programme. However, the programmes are often not functioning because of specific targets and activities are planned/implemented. Township family physicians do already hold monthly administrative meetings, but no time is spent on antibiotic prescribing peer-review discussions 2. Township hospital family physicians will prescribe antibiotics according to existing national guide on use of antibiotics which are not specifically designed for primary care facilities, and rarely used. Most physicians prescribe based on their group practice and existing knowledge/practices. Any messages given by control-arm family physicians will be at their own discretion based on their existing practice and training 3. Township hospital family physicians receive relevant medical training before they obtain their qualifications, but only a few of them have opportunities to receive continuing training afterwards and these trainings are usually not specifically for respiratory infections or antibiotics use. We will not provide any training to control-arm family physicians 4. Township hospitals already have a similar electronic prescription system in the EMR, but there is no clinical decision module, alarm system or pop-ups for recommended and non-recommended antibiotics. We will not make this available for control-arm hospitals
Consumer side (patients/caregivers)	1. Printed educational material and WeChat-app versions describing appropriate antibiotic use for respiratory infections will be available during the intervention period. These educational materials along with education videos will be accessible for the public in the township hospital public areas 2. Patients will be invited to scan a QR code to link their WeChat account to the township hospital public WeChat account for receiving health education materials, making queries and comments, and viewing suggestions about common queries	1. There are and will be no health education materials on appropriate antibiotic use available in control-arm hospitals 2. Currently, township hospital do not have WeChat public accounts for patients, so we will not implement them in control-arm hospitals

*ARI* acute respiratory infection, *EMR* electronic medical records, *RTIs* respiratory tract infections

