#### Primary outcome

Our primary outcome is the proportion of prescriptions for eligible patients (aged 0–75 years with a diagnosed ARI, excluding pneumonia and other complications – see the ‘Eligibility criteria’ section) that contain one or more antibiotics, which (as per related literature) we refer to as the antibiotic prescription rate (APR). As in previous trials [17, 34] we will use the APR to measure the proportion of unnecessary antibiotic prescribing/use, given that most patients with URTIs and acute bronchitis do not benefit from antibiotics.

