#### Secondary outcomes

We will also collect and create the following set of secondary outcomes, which will allow us to evaluate whether the intervention affects the proportion of antibiotic-containing prescriptions where the antibiotic(s) are of a specific class or method of delivery. The following set of indicators is based only on those eligible prescriptions containing at least one antibiotic: (1) the broad-spectrum antibiotic prescription rate: the proportion that contain one or more broad-spectrum antibiotics (we define broad-spectrum antibiotics as those antibiotics that act on the two major bacterial groups gram-positive and gram-negative, or any antibiotic that acts against a wide range of disease-causing bacteria); (2) the fluoroquinolone prescription rate: the proportion that contain one or more fluoroquinolone antibiotics; (3) the multiple antibiotic prescription rate: the proportion that contain two or more antibiotics of any kind; (4) the intravenously injected antibiotic prescription rate: the proportion that contain any antibiotics delivered by intravenous injection. As the intervention will address appropriate use of antibiotics for bacterial ARIs, we will also measure, taking the total number of antibiotics prescribed per township hospital as the denominator and (5) the proportion that contain any antibiotics in the *Access* group of the *WHO’s 2019 Essential Medicines List* classification [35]. As all these outcomes have denominators that only include eligible prescriptions containing one or more antibiotics, when analysed they will effectively be creating ‘outcome-based subgroups’ that are defined post randomisation [36]. This is a common, but often unrecognised, issue that can introduce bias into the treatment-effect estimates for such outcomes. However, there are no clearly applicable/feasible solutions for our situation [36], and so we will treat the results for these specific outcomes as exploratory.

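### Chest x-ray is prompted only in the intervention arm and a pneumonia diagnosis removes a prescription from the primary APR, so the denominator may differ by arm and the listed analyses could not show it

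*Protocol article*

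**What the plan says.** **Intervention arm.** Table 2 (Methods, Intervention) contains two x-ray prompts. Under the operational guidelines (item 2), "chest x-ray examinations will be recommended when symptoms indicate pneumonia but clinical signs are not severe", and also at a second visit with signs of pneumonia. Under the EMR changes (item 4b), an alarm flags a patient who re-visits within 14 days or has been admitted within a month for respiratory infection or sepsis: "In this scenario, chest x-ray and blood profile examinations will be recommended and recorded".

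**Control arm.** These hospitals "continue treating patients with ARIs according to their existing usual treatment practices and guidelines". In their EMR "there is no clinical decision module, alarm system or pop-ups for recommended and non-recommended antibiotics".

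**Eligibility and outcome.** Eligibility criteria (Patients) excludes "pneumonia, as it is severe and clinically challenging to group with other uncomplicated ARIs". The primary APR is computed on patients "with a diagnosed ARI, excluding pneumonia and other complications". Recruitment, randomisation and blinding states that providers cannot be blinded.

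**Related cautions.** Under Secondary outcomes, the protocol says that denominators defined after randomisation are an "issue that can introduce bias into the treatment-effect estimates for such outcomes", and treats the affected outcomes as exploratory. These are the outcomes restricted to antibiotic-containing prescriptions. The first limitation in the Discussion admits a possible arm imbalance from ICD-10 training given in one arm, but discusses it only for symptom-based diagnoses.

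**Data and analyses.** Data collection and management describes extracting the prescriptions of eligible patients. The sensitivity analyses listed under Statistical analyses vary the imputation and the covariate adjustment.

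**The concern.** The APR is meant to measure what physicians prescribe for uncomplicated ARI. Who counts as uncomplicated ARI is decided at the consultation, after randomisation, by a physician who knows the allocation and whose work-up for pneumonia the trial changes in one arm only. If the prompts change how often pneumonia is diagnosed, prescriptions enter or leave the denominator in one arm, and the APR can move without any change in prescribing.

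The protocol applies this reasoning to its antibiotic-restricted secondary outcomes but not to the pneumonia exclusion, which affects the primary outcome. Adjusting for the baseline APR does not help, because the labelling change would begin after randomisation. Imputation does not help either, because it acts only on prescriptions already judged eligible. What is at stake is how the size of the effect is interpreted: readers could not tell whether the denominators stayed comparable.

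**Working it through.** **Inputs from the protocol (Sample size):** control APR about 80%; target reduction 15 points, so 65% in the intervention arm; ICC 0.14 (intervention) and 0.09 (control); 500 prescriptions per hospital; 17 hospitals per arm; two-sided alpha 0.05; power 80%.

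**Inputs not in the protocol (assumed):** d, the share of ARI prescriptions in one arm that become pneumonia-coded, 1% to 5%; q, the share of those containing an antibiotic, 90% or 100%.

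**Step 1. The stated sample size.** Clusters per arm = (1.960 + 0.842)² × [0.80 × 0.20 × (1 + 499 × 0.09)/500 + 0.65 × 0.35 × (1 + 499 × 0.14)/500] / 0.15² = 7.849 × (0.01469 + 0.03224) / 0.0225 = 16.37. Rounded up, this is the stated 17. The point does not depend on this figure, but the result confirms how the inputs are used.

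**Step 2. Shift in one arm.** If a share d leaves an arm whose true APR is p, the observed APR is (p − dq)/(1 − d), so the shift is −d(q − p)/(1 − d).

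| q | p | d = 1% | d = 5% |
|---|---|---|---|
| 100% | 80% (no true effect) | −0.20 points | −1.05 points |
| 100% | 65% (target effect) | −0.35 | −1.84 |
| 90% | 80% | −0.10 | −0.53 |
| 90% | 65% | −0.25 | −1.32 |

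For example, 0.05 × 0.35/0.95 = 1.84 points. A share of 1% to 5% is 5 to 25 of 500 prescriptions per hospital, or 85 to 425 of 17 × 500 = 8,500 per arm.

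**Step 3. Direction (q = 100%).** The effect on the intervention-minus-control difference depends on which arm relabels more. Negative values exaggerate the reduction.
- Control arm only, 1% to 5%: +0.20 to +1.05 points.
- Intervention 5%, control 2%: −0.64 (no true effect) or −1.43 (target effect).
- Intervention 1%, control 3%: +0.42 or +0.27.

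**Step 4. Size against the test.** With no true effect, the SE of the difference is √[0.16 × (70.86 + 45.91)/8,500] = 4.69 points. From the noncentral t distribution with 31 df, two-sided type I error is 5.02%, 5.19% and 5.54% for shifts of 0.20, 0.62 (d = 3%) and 1.05 points. The largest shift in step 2 is 1.84/15 = 12% of the target. To produce a spurious 15 points from 80% by this route alone, d would have to be 0.15/(0.20 + 0.15) = 43%.

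**Step 5. Why a wider denominator answers the question.** With ARI and pneumonia prescriptions pooled, the APR is [(p − dq) + dq] / [(1 − d) + d] = p, where p is the rate before any relabelling. Moving a prescription from one label to the other leaves it unchanged.

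**The case against.** The strongest reply is that this belongs to the analysis plan. The protocol promises a full plan before the trial dataset is created, and a list of sensitivity analyses in an article need not be complete. That holds for the form of any added analysis, and it is why the point is rated low. What remains is that the protocol fixes a primary denominator which one arm's intervention can alter, and extends its own caution about such denominators only to secondary outcomes.

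Second, the mechanism is narrow. The alarm in item 4b acts on re-visits or after an admission, so the first prescription is unaffected; item 2 can also apply at a first visit, but only where symptoms point to pneumonia. Control physicians may order x-rays too, since the trial withholds only its own recommendation and alarm. This stands, and it limits the likely size.

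Three stronger readings are tempting, and the documents do not support them.
- *The bias favours the intervention.* A reader might infer this because the prompts act in one arm. But a negative x-ray can keep a patient in the ARI group whom a control physician would have called pneumonia on clinical grounds, and step 3 shows the sign reversing.
- *Physicians gain by relabelling.* Table 2 item 1c mentions "adjusting assessments for individual physicians based on their performance". Nothing says that pneumonia prescriptions fall outside peer review or assessment; only the trial outcome excludes them.
- *Pneumonia records will be unavailable.* The extraction is described for eligible prescriptions, but the same section has the team screening uncoded prescriptions and recording comorbidities in order to exclude, so it will see some excluded records. Stored re-visit and hospitalisation data give a further indirect check. No count of outpatient pneumonia prescriptions by arm is described, however.

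**Conclusion.** The point holds as a low-severity improvement. Eligibility for the primary APR depends on a post-randomisation diagnosis by unblinded physicians, and the trial changes the work-up for that diagnosis in one arm only, so the denominator may differ by arm. The direction is open. Under assumed relabelling of 1% to 5% in one arm, with every moved prescription containing an antibiotic, the shift is about 0.2 to 1.8 points, and it is smaller if fewer of them do. The upper end applies only when the full 15-point effect is real. A reader might infer that the primary test is compromised; it is not, since type I error stays at or below about 5.5% under these assumptions. What the listed analyses cannot do is separate a change in prescribing from a change in labelling. More correct diagnosis of pneumonia, or an antibiotic avoided after testing, is a legitimate result of the programme, so the primary analysis should stand.

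**What to change.** 1. Define the EMR request as outpatient prescriptions with a primary diagnosis of ARI or pneumonia, in both arms and for both the baseline and the trial period. The baseline period is needed because the two-stage method adjusts for each hospital's baseline value of the outcome.
2. Report the pneumonia-coded share of these prescriptions by arm and period.
3. Pre-specify one sensitivity analysis of the APR that includes pneumonia-coded prescriptions in both arms and uses the same two-stage method. Leave the primary analysis unchanged.

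The cost is one wider query to the Prefecture Health Information Centre, one descriptive row and one extra analysis, with no new hospitals, patients or visits. The sensitivity APR will include prescriptions for which an antibiotic is appropriate, so it serves only as a check on the between-arm difference and not as a second estimate of unnecessary prescribing. Because the analysis plan precedes the dataset, there is still time to make the change.
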